### ***Inclusion and exclusion criteria***

Children of either sex aged 3-59 months of age at the start of each period of drug administration will be eligible for inclusion in the trial, provided that parental consent is obtained. Children under the age of three months on the date of the start of drug administration will be excluded that year, as SMC is not recommended for children in this age group whose risk of acquiring malaria is low. Children who reach the age of 59 months or more at the end of the first or second years of treatment will not receive SMC in subsequent years. Exclusion criteria will be as limited as possible to make the results of the trial broadly applicable and will include i) a severe, chronic illness, ii) a known allergy to one of the study drugs, iii) known HIV positive subjects using Cotrimoxazole. [Children with acute clinical malaria at the time of SMC drug administration will be treated by ACT and will not be given SMC drugs during that round as per WHO recommendation. They will receive SMC drugs during subsequent cycles.](#)

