## 2. Background

More than 200 million people live in areas where malaria transmission is highly seasonal. Malaria remains a major cause of morbidity and mortality and is estimated to cause between 610 000–971 000 deaths globally per year. Sub-Saharan Africa is disproportionately affected, suffering 91% of global malaria deaths with 88% occurring in children under 5 y of age [WHO 2012]. In absence of a vaccine, simple and effective control strategies are urgently needed to reduce the malaria burden in sub-Saharan Africa. Vector control, using insecticide-treated bednets (ITNs), insecticide-treated curtains, or indoor residual spraying (IRS), can reduce mortality and morbidity from malaria substantially [Lengeler 2004], but in high transmission settings, these interventions provide only partial protection and additional control measures are needed.

We recently showed that Seasonal Malaria Chemoprevention (SMC), previously known as Intermittent Preventive Treatment of Malaria in children, reduces malaria infection and disease by more 80% in Malian children, prompting the WHO to approve SMC as policy for Sahelian countries in March 2012 [Dicko et al 2011, WHO GMP 2012]. SMC consist of of the administration of full treatment courses of an antimalarial medicine during the malaria season to prevent malarial illness with the objective of maintaining therapeutic antimalarial drug concentrations in the blood throughout the period of greatest malarial risk. The WHO recommendation states that complete treatment course of Sulfadoxine-pyrimethamine plus Amodiaquine (SP+AQ) should be given to children aged between 3 and 59 months at monthly intervals, beginning at the start of the transmission season, to a maximum of four doses during the malaria transmission season [WHO GMP 2012].

The strategy has been shown to be highly effective, safe and cost-effective for preventing malaria in children under 5 years of age in areas with highly seasonal malaria transmission such as the Sahel region in Africa [WHO GMP 2012].

Although several potential approaches can be used to implement the strategy, there is insufficient evidence to recommend a standard strategy to deliver SMC [WHO implmentation guidelines]. Two studies have compared the delivey of SMC through community health workers and health facilities in Ghana and The Gambia [Kweku et al 2009; Bojang et al 2011]. In the Gambia, higher coverage of SMC was found when SMC is delivered through community health workers

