**B. Study Outcome measure(s)**

The primary outcomes are:

1. SMC coverage for the determination of the optimal mode of delivery during Year 1. SMC coverage will be defined as proportion of the children who have received the three treatments doses at each of the three rounds of SMC.
2. Incidence of the clinical malaria for the optimal frequency of SMC in Year 2. Clinical malaria will be defined as signs and symptoms suggestive of malaria with positive RDT and/or positive blood smear.

Secondary trial outcomes of the study include:

1. Parasite prevalence defined as the proportion of children with a positive malaria blood smear and parasite density measured in Years 1, 2 and 3.
2. Prevalence of moderate anemia defined as hemoglobin concentration < 8 g/dL measured by hemoglobin analyzer.
3. Cellular and humoral antimalarial immune responses to malaria parasites.
4. Levels of cytokines and other host responses measured in sera/plasma or in immune cells.

5. Frequency of mutations at codons 51, 59, and 108 of the dhfr gene, 437 and 540 of the dhps gene, codon 76 in the *P. falciparum* chloroquine transporter gene (pfcr), and codon 86 of the *P. falciparum* multidrug resistance gene one (pfmdr1)

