#### ***Census and randomization***

Once community consent to the trial is obtained, a household census will be conducted and all households within the study areas with children under 5 years of age will be identified. At the time of census, a preliminary screening of potentially eligible children will be undertaken. Eligible children will be identified and written informed consent will be obtained from their caretakers for their inclusion in the trial. Children entered into the trial will be assigned a unique ID number and their demographic data (date of birth and/or age, and gender) will be collected.

The census will be updated at each SMC round and potentially eligible participants (such as children who did not reach the age of three months during the previous round) will be identified and screened for eligibility and enter into the study. This updated census will collect information on migration and death of children enrolled into the study for precise estimation of person-time of follow-up.

The unit of randomization will be village and all eligible children in a village will be allocated to the same study arm (DDD+ DOT or DDD+NDOT or FPD+ DOT or FPD + NDOT) to avoid confusion in Year 1. Villages in the selected sub-districts will be randomized at 1:1 ratio to receive either a door –to-door delivery (DDD) or fixed point distribution (FPD) of SMC. They will also be randomized to receive SMC as directly observed therapy (DOT) or a non-directly observed therapy (NDOT). In Year 2, villages in the two newly randomly selected districts will be randomized into two groups to receive either three or four rounds of SMC.

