### ***Interventions***

SMC will consist of the administration of full treatment courses of sulfadoxine-pyrimethamine plus amodiaquine (SP+AQ) at monthly intervals during the peak of the malaria transmission season (August – through October or November depending on the year of the study and study arm). During each round, children aged 3–11 months will receive 75 mg of AQ given once daily

for 3 days plus a single dose of 250/12.5 mg of SP, while children aged 12–59 months will received 150 mg AQ base given once daily for 3 days and a single dose of 500/25 mg of SP. The single dose of SP will be given only on the first day, at the same time as the first dose of AQ. Children will be observed for 30 minutes after drug administration. If vomiting occurs during this period, drugs will be re-administered. If vomiting recurs this will be noted but the drugs will not be given on a third occasion. Such children will not be excluded from the trial and they will be eligible to receive drugs at the subsequent monthly treatment.

In villages assigned to door –to-door delivery (DDD), community health workers (CHW) will visit each compound to administer SMC drugs. In the villages assigned to fixed point distribution (FPD), children will receive SMC at a central fixed point in the village. The administration of the three days treatments at each round will be done by the CHW for children assigned to directly observed therapy (DOT) while for children assigned to non-directly observed therapy (NDOT), the treatment of first day will be given by the CHW and treatments for second and third days will be given by the caregiver at home for each round. SMC will be implemented using standardized field implementation guidelines developed by the WHO [WHO 2013] adapted to the situation in Mali. Monitoring and evaluation tools for SMC will be developed and integrated with the health system in Mali.

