## 5. Statistical Considerations and Data Analysis

### A. Sample Size and Power Calculation(s)

*Cross-sectional surveys.* Sample size for cross-sectional surveys will be based on the SMC coverage. Assuming 60% average coverage of SMC by the combination of nonoptimal methods (pools of two groups), 300 children/arm will be needed to detect 10% increase in average coverage for two pooled groups with at least 85% power correcting for multiple tests and using two Fisher's exact tests. To account for cluster sampling with a minimum 10 clusters per arm, interclass correlation of 0.01 (based on a previous trial showing vaccine coverage (Dicko et al BMC Pub Health 2011), and 5% missing data, 446 children will be surveyed per group (total of 1784 children).

*Passive surveillance.*

Assuming a clinical malaria attack rate of 0.3 per child per year in “3 rounds” arm, to detect an absolute difference in attack rate of the 0.075 episode/chil/ year (corresponding to 25% reduction) in the “4 rounds” arm, with a one sided p-value of 0.025 and power of 80%, using a quasi poisson model accounting for 20 equally sized clusters per arm with intraclass correlation of 0.01 and 5% missing data we will need 1386 per arm, or 2,772 subjects total.

*Immunological parameters.* We will base our sample size calculations for immunological endpoints on the humoral immune response to AMA1. We select this response because AMA1 is highly immunogenic from among malaria antigens. Also, the intervention in this trial is directed at reducing the blood stage burden of parasites during the malaria season, and the response to AMA1 reflects exposure to blood stage forms of the parasite. In earlier serology studies of young children participating in an AMA-1 vaccine trial in Bancoumana, Mali (Sagara et al, Vaccine, 2009), we observed the peak antibody titer against AMA1 to occur near the end of the malaria season (among children receiving control vaccine), with geometric mean antibody levels of 120 antibody units (95% CI, 70-205). Antibody levels just prior to the start of the malaria season (before vaccination) were 40 (25-75) antibody units. Based on these data, 467 subjects per

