### **C. Final Analysis Plan**

*Describe statistical methods that will be used to analyze data.*

Data will be entered and verified using DataFax. The cleaned database will be exported to Stata (Houston Texas USA) or SAS for analysis. An intention-to-treat analysis will be used except for the immunological endpoints for which the exact number of the SMC treatments received will be considered.

SMC coverage will be determined using the information on the SMC card and from interview of parent or care giver and will be determined as the proportion of children who received all the treatments at all the SMC rounds during the transmission season. The proportion of children who received at least the first treatment dose of the SMC will be also estimated as secondary endpoints for SMC coverage. SMC coverage will be compared between arms and years of

interventions with 95% confidence intervals adjusted for cluster design (using cluster option in Stata for example). The DDD+NDOT arm will be considered as control group.

The census of the children will be updated at each round and at the end of the transmission season to allow a good estimation of person-time of follow-up. Cases of the clinical malaria will be recorded and the incidence rate of the clinical malaria defined as the number of clinical malaria episodes divided by total child days at risk. Children will not be considered at risk 21 days after a clinical malaria episode. Incidence rates of clinical malaria will be compared between treatment arms using generalized estimating equation to estimate the incidence rate ratio, with adjustment for age, previous SMC regimens and the lack of independence among repeated episodes in the same child.

Proportions of other secondary endpoints such as parasite prevalence, prevalence of anemia and frequency of molecular markers of resistance to SP and AQ and adverse events associated with study drugs will be estimated and compared between groups using generalized linear models with 95% confidence intervals, adjusted for cluster design and potential confounding variables such as age and use of ITN.

Differences at baseline will be compared using Chi-squared or Fisher's exact tests as appropriate for categorical variables and by analysis of the variances for quantitative variables that are normally distributed. Nonparametric tests will be used for non-normally distributed data.

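### The English eligibility text bars infants under three months at the start of dosing for the whole year, while the census section enters them at the first monthly round after they reach that age

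*Protocol*

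**What the plan says.** The English section on inclusion and exclusion criteria (under 4. Study Design) admits children aged 3-59 months at the start of each period of drug administration, without defining that period. The next sentence reads: "Children under the age of three months on the date of the start of drug administration will be excluded that year". Later in the same paragraph, a child with acute malaria "will not be given SMC drugs during that round as per WHO recommendation" and resumes at later cycles.

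The section on census and randomization has the census updated at every SMC round. It gives as its example of newly eligible participants "children who did not reach the age of three months during the previous round) will be identified and screened for eligibility", who then enter the study. Under Interventions, rounds are given "at monthly intervals during the peak of the malaria transmission season", from August to October or November.

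The French text has the same round-by-round entry in section 4.4. Its section 4.5 adopts the WHO eligibility criteria and says that children under three months at the start of administration are not included, without extending this to the year.

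Section 3.B defines Year 1 coverage as the "proportion of the children who have received the three treatments doses at each of the three rounds of SMC". Section 5.C has it "determined as the proportion of children who received all the treatments at all the SMC rounds during the transmission season". Neither section says whether a child who enters after round one belongs in the denominator.

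**The concern.** Both English sections instruct field staff, and they give opposite answers for the same child. Under the eligibility sentence, an infant who turns three months between the August and September rounds gets no SMC until the next season and misses two of three rounds, or three of four in the four-round arm of Year 2. Under the census section the same infant is dosed in September. Villages could apply different rules in good faith.

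A secondary question follows. A child who enters at round two or three cannot have received every dose at every round, whatever the delivery method. If such children are counted in the coverage denominator, they can only be scored as not covered.

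**Working it through.** **1. The texts applied to one child** (two months old at the August round, three months old by September)

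| Section | September round |
|---|---|
| English, inclusion and exclusion criteria | barred until next season |
| English, census and randomization | screened and entered |
| French 4.4 | screened and entered |
| French 4.5 | not included at the start of administration; no duration given |

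Three readings might reconcile the English sections:
- *The year means the round.* The same paragraph names a single round when it means one (the acute-malaria rule), so the two terms are kept apart.
- *The census rule applies only from one season to the next.* This is strained, because the update is done at each round and rounds are a month apart.
- *Each period of administration means each round.* Even so, the exclusion sentence then attaches a year's bar to it.

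**2. Size of the group.** The protocol gives no age distribution, so even monthly age bands are assumed. Ages 3-59 months give 57 bands at round one, and two further bands reach three months by round three.
- Share of enrolled children: 2/(57 + 2) = 2/59 = 3.4%.
- Range if the two entering bands hold 0.75 to 1.5 times the average: 1.5/58.5 = 2.6% to 3/60 = 5.0%.
- Survey of 446 per arm: 446 × 2/59 = 15.1 (11.4 to 22.3). Survey of 1,784 in total: 60.5 (45.7 to 89.2).

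**3. The plan's own figure.** Section 5.A needs 300 children per arm before clustering and surveys 446, with 10 clusters per arm, intraclass correlation 0.01 and 5% missing data.
- Analysed: 446 × 0.95 = 423.7 per arm, or 42.37 per cluster.
- Design effect: 1 + (42.37 − 1) × 0.01 = 1.414.
- Effective size: 423.7/1.414 = 299.7 per arm, which reproduces the 300. Pooling two arms gives 600 against 600.

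**4. Effect on coverage, if late entrants are in the denominator and the planning values of 60% and 70% describe children eligible at round one.**
- 0.60 × 57/59 = 58.0%, and 0.70 × 57/59 = 67.6%.
- The difference falls from 10 to 9.7 points (9.7 to 9.5 over the range in step 2).

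**5. Effect on power.** Section 5.A names two Fisher's exact tests with a correction for multiplicity. The size of the correction is not stated; two-sided 0.025 per test is assumed. Exact power at 600 against 600:
- 60% vs 70%: 91.0%.
- 58.0% vs 67.6%: 87.9%.
- Over the range of shares: 88.6% (2.6% late entrants) to 86.4% (5.0%).

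All values exceed the stated 85%.

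**6. Restricting the denominator to children age-eligible at round one.**
- 446 × 57/59 = 430.9 per arm; × 0.95 = 409.3.
- Design effect: 1 + (40.93 − 1) × 0.01 = 1.399. Effective size: 409.3/1.399 = 292.5 per arm.
- Pooled 585 against 585 at 60% vs 70%: exact Fisher power 90.2%.

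**The case against.** The strongest reply is that this is a drafting slip of two words. The census section names exactly this group as its example, the intervention follows WHO field guidelines, and the French text has no year-long bar. In practice infants would probably be dosed from the first round at which they qualify. This stands as an argument about what was intended, and it shows which sentence to change. It does not remove the contradiction, because the exclusion criterion is explicit and someone applying it literally would withhold the drug.

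A reader might infer that the primary coverage outcome certainly counts late entrants as failures and loses power. The documents do not support that. Neither coverage definition states the denominator, which may properly be left to the statistical analysis plan. The 60% in section 5.A may already describe the whole surveyed population, in which case deducting late entrants again would count them twice and the power loss disappears. The coverage effect is therefore conditional.

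The WHO schedule in section 2 ("should be given to children aged between 3 and 59 months at monthly intervals, beginning at the start of the transmission season") is also weak support. It gives an age range and an interval, and is silent on a child who qualifies mid-season. The case rests on the census section and its French counterpart.

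Finally, restricting the denominator does not deal with children who miss a round because of acute malaria. They also cannot meet the all-rounds definition. That is true, and the restriction should not be presented as a complete repair of the outcome.

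**Conclusion.** The English exclusion sentence is wrong as written. It contradicts the English census section and the French section 4.4, and no reading reconciles them without strain. The point is minor, but it settles whether infants who turn three months mid-season receive SMC that season.

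The group is about 3.4% of enrolled children over three rounds (2.6% to 5.0%), resting on the assumed age bands. The coverage consequence is secondary and holds only if late entrants are counted in the denominator: about 2 points lower in all arms (2.0 at 60%, 2.4 at 70%). The fall in Fisher power from about 91% to 88% needs the further assumption that the planning values refer to children eligible at round one.

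A reader might also infer a distorted comparison of delivery methods. The documents give no ground for that: randomization is by village, the age rule is the same in all four Year 1 arms, and late entrants fail the all-rounds definition under any method. No bias between arms is claimed.

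**What to change.** In the English section on inclusion and exclusion criteria, replace the year-long exclusion with: *will not receive SMC at that round and become eligible at the first round at which they are three months old*. Add a matching clarification to the French section 4.5. This costs two sentences and no extra visits, since the census is already updated at each round.

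Secondarily, state in sections 3.B and 5.C, or in the statistical analysis plan, that all-rounds coverage is reported among children age-eligible at the first round of the season. The cost is a denominator about 3.4% smaller (446 becomes about 431 per arm, Fisher power about 90%), and this coverage figure no longer describes late entrants.

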### ***Interventions***

SMC will consist of the administration of full treatment courses of sulfadoxine-pyrimethamine plus amodiaquine (SP+AQ) at monthly intervals during the peak of the malaria transmission season (August – through October or November depending on the year of the study and study arm). During each round, children aged 3–11 months will receive 75 mg of AQ given once daily

for 3 days plus a single dose of 250/12.5 mg of SP, while children aged 12–59 months will received 150 mg AQ base given once daily for 3 days and a single dose of 500/25 mg of SP. The single dose of SP will be given only on the first day, at the same time as the first dose of AQ. Children will be observed for 30 minutes after drug administration. If vomiting occurs during this period, drugs will be re-administered. If vomiting recurs this will be noted but the drugs will not be given on a third occasion. Such children will not be excluded from the trial and they will be eligible to receive drugs at the subsequent monthly treatment.

In villages assigned to door –to-door delivery (DDD), community health workers (CHW) will visit each compound to administer SMC drugs. In the villages assigned to fixed point distribution (FPD), children will receive SMC at a central fixed point in the village. The administration of the three days treatments at each round will be done by the CHW for children assigned to directly observed therapy (DOT) while for children assigned to non-directly observed therapy (NDOT), the treatment of first day will be given by the CHW and treatments for second and third days will be given by the caregiver at home for each round. SMC will be implemented using standardized field implementation guidelines developed by the WHO [WHO 2013] adapted to the situation in Mali. Monitoring and evaluation tools for SMC will be developed and integrated with the health system in Mali.

### **Follow-up and measurement of outcomes**

Surveillance for clinical attacks of malaria will start at the time of the first administration of study drugs in August and continue until the end of the third malaria transmission (November/December 2016). Clinical episodes of malaria will be detected using a passive surveillance system. Data will be collected by health care workers including the community health workers. Clinical malaria episodes occurring in the study health facilities or in the study communities will be recorded throughout the study period in all the study villages. Children with an illness suggestive of malaria will be tested for malaria with RDT and/or with blood smear by the health center staff and/or community health workers and treated according to the recommendations of the National Malaria Control Program. Cases of clinical malaria will be recorded on standardized case report forms. Refresher training of staff will be conducted each

year to ensure standardization in the recording of symptoms and signs that are used to make a diagnosis and categorisation of clinical malaria episodes.

Each year, at the onset and the end of malaria transmission season, a cross-sectional survey will be undertaken in a random sample of children to assess the prevalence of malaria infection, anemia and immunological parameters. Coverage of SMC will be assessed at the cross-sectional survey at the end of the transmission seasons through interview of the caregivers and based on information in the child SMC administration card. Children will be examined, and a blood sample will be obtained for measurement of including hemoglobin concentration, preparation of a blood smear for microscopy, and analysis of cellular and humoral immune responses to known (CSP, MSP1, AMA1) and novel liver and blood stage *P. falciparum* antigens.

